### Statistical plan

The analysis plan for the PRAISE study aims 1) and 2) is outlined in Fig 1.

**Fig 1 pone.0257361.g001:**
[figure not shown]

### Aim 1: AI algorithms for fracture and treatment characteristics

For eligible ED, short stay unit and VOTOR registered distal radius fracture cases, the pre- and post-treatment X-ray images, radiology reports and surgical reports (where applicable) will be obtained for AI analysis. A multimodal deep learning fracture reasoning system will be developed that reasons jointly on X-rays and clinical text. The analysis will occur in three stages (Fig 1).

In *Stage 1*, we will develop specialised language representation models akin to Bert (Bidirectional Encoder Representations from Transformers) [37–39] called Fracture-Bert to generate bidirectional word representations that captures information related to specific distal radius fracture characteristics and treatment for the classification task. The X-ray images will be classified with deep CNN models [40, 41], where we pass each image through a series of fully-connected convolutional layers to learn features of various aspects of the X-ray image.

*Stage 2* will build a novel deep multimodal learning architecture that uses joint visual-linguistic representation learning from paired vision-linguistic data (i.e. paired medical images and radiology/operative text reports) to preserve and fuse semantics across modalities. Fracture reasoning will discriminate different fracture objects based on the learned latent representations. The pretrained architecture will use a variety of large external resources to complement the existing hospital data inputs and enhance the neural networks to improve predictions and advance learnings of fracture data.

*Stage 3* extends the models developed in Stages 1 and 2 to boost the model interpretability with background medical knowledge to highlight the key distal radius fracture features. The extended models with the attention mechanism [42, 43] will automatically attend to key phrases while predicting the corresponding fracture types. Salient fracture features will be assigned weights to generate the unimodal/multimodal representation. Learned attention weights will enhance our understanding of the key distal radius fracture characteristics and their treatment.

Fracture features will be categorised as present or absent based on the X-rays and radiology reports: radial height, radial inclination and ulnar variance; palmar inclination and teardrop angle; degree of comminution, etc. Treatment will be categorised into one of five categories: (1) closed reduction and immobilisation, (2) external fixation, (3) percutaneous wire fixation, (4) open reduction and internal fixation (plate), or (5) wrist fusion. Identification of surgical management and implant type from the X-ray images and operative report will be compared against the VOTOR implant data which is obtained from hospital ordering systems. Ordering systems currently are the most consistently available data source for orthopaedic trauma implants but the information extracted is highly variable, complete for only 60% of surgical cases, and does not specifically link implants to injury. VOTOR cases and ED presentation cases only will be compared for patient and fracture characteristics.

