## Introduction

Fractures are the most common form of hospitalised trauma, contributing to approximately 200,000 hospitalisations and over one million bed-days in Australia each year [1]. Distal radius fractures are the most common fracture of the upper limb across all age groups [2], second only to hip fracture as the primary reason for admission to hospital for fracture [3]. More than 400,000 people in England were admitted to hospital with a distal radius fracture over a 10-year period [4]. Six percent of women will have sustained a distal radius fracture by 80 years of age [5]. Of concern, the incidence of these fractures is increasing [3, 4]. In the UK, distal radius fracture admissions rose by more than 80% from 2004/05 to 2013/14 [4], while a previous Australian study projected a similar increase to 2021 based on figures from 1997 [6].

Distal radius fractures occur across all ages and are sustained in a range of high (e.g. motor vehicle collision) and low (e.g. fall on an outstretched hand) energy mechanisms and there many operative and non-operative treatment options. Surgery carries inherent risks for the patient and considerable cost implications based on the treatment choice and implant used. While most orthopaedic societies have established distal radius fracture management guidelines, adherence to guidelines is variable, even within a single country [7]. Data from Ireland from 2008 to 2017 showed a significant rise in the rate of plate fixation and a reduction in the use of percutaneous k-wires [8], despite economic analysis showing plate fixation was unlikely to be cost-effective if the fracture can be treated with a closed reduction [9]. In the US, surgical management was found to agree in only 40% of cases where the guidelines recommended nonoperative treatment [10]. A recent meta-analysis of 38 clinical trials favoured plate fixation for early and sustained functional recovery and lower rates of complications, although these studies focused on a single sub-type of distal radius fracture [11]. The authors observed variability in the populations studied, the numbers randomised, the treatments compared, and the outcome measures used, and they were unable to provide definitive treatment directives [11].

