### Data sources

The PRAISE study will use four data sources: 1) VOTOR registry patient data; 2) ED patient data; 3) SSU patient data; and 4) linked VOTOR patient data. Data sources 1) to 3) will be used to achieve study aim 1) and data source 4) will be used to achieve study aim 2).

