#### 1) VOTOR registry data

The VOTOR registry is the largest and most comprehensive orthopaedic trauma outcomes registry worldwide and is compliant with the ACSQHC operating principles for clinical quality registries. For patients hospitalised >24h for their wrist fracture, cases will be identified through VOTOR using the relevant ICD-10-AM diagnosis codes for the admission. Demographic, injury event, injury diagnosis (ICD-10-AM), procedures (ACHI), in-hospital outcomes, limited implant data, X-ray images, text reports from radiology and surgery, and patient-reported outcome measures (PROMs) will be extracted for all eligible patients for this study. The PROMs are collected prospectively via telephone interview at 6-, 12- and 24-months post-injury [34], and include the 12-item World Health Organization Disability Assessment Schedule (WHODAS), 5-level EQ-5D (EQ-5D-5L), numerical rating scale for pain, pain location, return to work and work disability questions. Follow-up rates exceed 80% at each time point. Linkage with the Victorian Registry of Births, Deaths and Marriages (VBDM) is used to identify post-discharge deaths.

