#### 3) Linked VOTOR data

The VOTOR registry data and data generated from the AI models in aim 1) for VOTOR cases will be sent to the Centre for Victorian Data Linkage (CVDL) for linkage with the Victorian Admitted Episodes Dataset (VAED) and the VEMD to provide admissions and ED presentations for the two years prior, and all admissions and ED presentations in the two years following, the VOTOR admission. This linked dataset will provide a comprehensive dataset for the prediction models, and will contain detailed descriptors of the fracture including fracture pattern, soft tissue injury and treatment, as well as demographic details, pre-existing health conditions, injury event details, treating healthcare service, and associated injuries.

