### Power calculations

A random sample of 517 patient sets of X-ray and radiology reports, proportional to fractures admitted to hospital with fractures managed in the ED or short stay unit, will be selected for classification by an orthopaedic surgeon, to quantify the agreement between the AI techniques and human assessment [35]. This is based on the diagnostic test with a null hypothesis of 0.7, alternative hypothesis of 0.8, power>0.8 and prevalence of dorsal displacement type fractures of 30% [36]. Class probabilities from the fracture classification will be generated and compared with orthopaedic surgeon assessment of the images and reports (gold standard). Key fracture words/phrases in text and regions in images, correlated with the predictions, will be highlighted with attention weights using a visualisation interface for surgeons to review the results generated by the models. We will retain 20% of the collected visual-linguistic fracture data pairs from training to test the proposed models. More than 6,000 VOTOR and 4,000 ED only cases will be available for the study, making the sample size more than sufficient to meet aim 2 of the study.

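### The one-of-five treatment list is not exhaustive for the ED and short-stay cases in Aim 1: immobilisation without reduction has no code

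*Protocol article*

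**What the plan says.** The rule stands in the section on Aim 1 (AI algorithms for fracture and treatment characteristics): "Treatment will be categorised into one of five categories: (1) closed reduction and immobilisation, (2) external fixation, (3) percutaneous wire fixation". The list closes with "4) open reduction and internal fixation (plate), or (5) wrist fusion". It has no class for other, none or combined treatment. The list of fracture features just before it is left open-ended; this one is not.

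The same section defines the cases: "For eligible ED, short stay unit and VOTOR registered distal radius fracture cases, the pre- and post-treatment X-ray images, radiology reports and surgical reports". On numbers, the Power calculations section says: "More than 6,000 VOTOR and 4,000 ED only cases will be available for the study". It gives no separate count for short-stay cases.

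The Data sources section assigns data to aims: "Data sources 1) to 3) will be used to achieve study aim 1) and data source 4) will be used to achieve study aim 2". Source 4 is the linked VOTOR dataset, which "will contain detailed descriptors of the fracture including fracture pattern, soft tissue injury and treatment". The registry section defines the admitted group: "For patients hospitalised >24h for their wrist fracture, cases will be identified through VOTOR using the relevant ICD-10-AM diagnosis codes".

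**The concern.** A single-label scheme works only if every case fits one class and only one. The Introduction itself says that there are "many operative and non-operative treatment options", yet the scheme offers one non-operative class and makes closed reduction part of it. The study adds ED-discharged and short-stay patients to the registry cases, and some of these may well have been immobilised without any reduction.

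Identifying treatment details validly is part of the first study aim. The article also argues that routine coding describes fracture management too broadly. If unreduced fractures are filed with reduced ones, or left out, the new treatment variable loses a distinction of the kind it is meant to add. Accuracy, precision or recall computed against labels built on this list would not show the problem, because the error would sit in the reference labels as well.

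**Working it through.** The article states no figure on treatment mix, so there is none to reproduce. Its validation sample of 517 is sized for agreement on fracture classification and does not bear on this point.

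**Step 1: test the list against treatment patterns.** The patterns are examples. The fit follows from the wording of the five classes.

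| Treatment received | Classes that fit |
|---|---|
| Closed reduction, then immobilisation | 1 |
| Immobilisation, no reduction | none |
| External fixator alone | 2 |
| Percutaneous wires alone | 3 |
| Plate | 4 |
| Internal fixation by screws without a plate | none |
| External fixator plus wires | 2 and 3 |
| Wrist fusion | 5 |

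The article's own background text, under Maximising the use of unstructured data, names screws and wires beside plates as fracture implants. It also treats type of reduction and use of fixation as separate attributes of management. The five classes merge the two.

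**Step 2: are such cases in scope?** For Aim 1, yes: ED and short-stay cases are included by name. For Aim 2, ED-only cases are not: it uses only the linked VOTOR data, and VOTOR cases are patients hospitalised for more than 24 hours.

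**Step 3: is the treatment label carried into Aim 2?** The text is not uniform. The statement of aims and the description of the linked dataset both include treatment. The Aim 2 methods name only fracture probabilities and classes as the AI output added to the registry data.

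**Step 4: possible size.** The counts of 6,000 and 4,000 come from the Power calculations section. Every share below is an assumption.

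- Aim 1, ED-only cases immobilised without reduction, 10% to 70%: 0.10 × 4,000 = 400 and 0.70 × 4,000 = 2,800. Against 6,000 + 4,000 = 10,000 cases, that is 4% to 28%.
- Aim 2, direct contribution of ED-only cases: 0.
- Aim 2, VOTOR cases, with 1% to 10% having combined or sequential treatment and 0% to 10% immobilised without reduction: (0.01 + 0.00) × 6,000 = 60 and (0.10 + 0.10) × 6,000 = 1,200, or 1% to 20% of 6,000. This applies only if the treatment label is used there.

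The ranges are wide because the article does nothing to narrow them. They show what the rule could affect, not what it will affect.

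**The case against.** The strongest reply has four parts.

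- **The fuller protocol may settle it.** The article does not say whether the label belongs to a patient, an episode or a procedure, nor whether it means initial or definitive treatment. A hierarchy for combined fixation could sit in a labelling manual. This stands for combined and sequential treatment, so the lack of a precedence rule is not charged as an error. It does not help the unreduced fracture: no hierarchy among five classes supplies a class that is absent.
- **No stated analysis scores a treatment label for ED-only cases.** The one stated check on treatment compares surgical management and implant type with VOTOR implant data, and the surgeon comparison concerns fracture classification. ED and short-stay data also include a separate treatment classification item. This stands against any claim that wrong labels will demonstrably be scored. It also means that no stated check would reveal a fault in the non-operative class.
- **Aim 2 is largely protected.** ED-only cases are outside it, fracture features are coded separately, and registry procedure codes already record reduction type and use of fixation. This stands.
- **Nothing shows how many cases are affected.** This also stands.

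A reader might infer that a large share of cases must be mislabelled in both aims. The documents do not support that. They give no treatment frequencies, cases that do not fit might be left unclassified, and the group in which immobilisation without reduction seems most likely does not enter Aim 2.

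**Conclusion.** The point holds in a limited form. As written, the five-class rule is not exhaustive for the Aim 1 population. Immobilisation without reduction and internal fixation other than by plate have no valid code, and combined fixation can fit two. This follows from the stated list and does not depend on any assumed frequency.

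The size is unknown; the 4% to 28% for Aim 1 is illustration only. Any effect on Aim 2 is confined to admitted VOTOR cases and depends on the treatment label being carried forward, which the aims and the linked-data description suggest and the Aim 2 methods do not state. It is a defect in the coding frame, worth correcting before labelling. It changes no sample size and implies no view on which treatment is right.

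**What to change.** Before labelling starts, do one of the following:

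- keep one variable and add classes for immobilisation without reduction, combined treatment, and other or not determinable; or
- record each component as a yes/no flag: reduction, immobilisation, external fixation, wires, plate, other internal fixation, fusion.

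In either case, state whether the label refers to initial or definitive treatment. Use the same coding in the comparison with VOTOR implant data and in any Aim 2 model that includes treatment, and say in the Aim 2 methods whether treatment is carried forward.

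The cost is a revised coding frame. Some classes will be sparse and may need pooling in the models; pooling rules are best set before outcomes are examined.

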### Aim 2: Prediction modelling

The performance of models including the AI predicted indicators from the deep learning models will be tested against models including standard registry information using the linked VOTOR registry data (data source 4)). The capacity of the AI indicators to predict outcomes of clinical and post-operative complications, and PROMs post-injury. This will enable us to determine which radiological features based on the X-rays and text reports improve prediction over the standard data available in the registry. AI-derived fracture predicted probabilities and classes will be added to the VOTOR registry data and sent to the CVDL for the Linked VOTOR data. This linked dataset will provide a comprehensive longitudinal dataset for the prediction models.

The capacity of the AI derived fracture characteristics to predict outcome compared to the Linked VOTOR registry data alone will be tested using the following outcomes:

Fracture management complications: implant failure; non-union; mal-union of the fracture; infection; neurological injuryReadmission to hospital for fracture managementPresentation to the ED for fracture-related issuesPatient-reported outcomes at 6-, 12-, and 24-months after injury: EQ-5D-5L; 12-item WHODAS; pain scores; return to work and work-related disability.

A systematic approach to variable selection and model predictive performance will be implemented (Fig 1). Models will investigate predictive pathways and risk of outcomes of interest. State of the art longitudinal machine learning (ML) models [44] will be used for both the variable selection and prediction stages. The large number of covariates raise potential multicollinearity issues, and the possibility of unstable estimates. Therefore, where applicable a number of ML penalized regression methods will be implemented to reduce covariate numbers. The analyses will account for correlated and clustered responses to perform the variable reduction and prediction tasks.

Linear and generalized linear mixed models (LMMLasso/GLMMLasso) [45], longitudinal multi-level factorization machines model (LMLFMM) [46], longitudinal support vector regression (LS-SVM) [47] and mixed effects random forest (MERF) [48] will be used as these machine learning techniques can handle longitudinal data and a large number of potentially correlated features. The inclusion of predictions from Aim 1 will incorporate associated error that potentially compounds further error with their inclusion in the predictive models, so we will use several measures to review model performance. All models will be summarised by the predictive performance measures of accuracy, precision and recall [49] to select the best performing model for each outcome, and quantify the impact of the inclusion of the AI variables over registry data alone.

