**Methods and design:**

Adult (16+ years) patients presenting to the emergency department, treated in a short stay unit, or admitted to hospital for >24h for management of a wrist fracture in four Victorian hospitals will be included in this study. The study will use routine registry data from the Victorian Orthopaedic Trauma Outcomes Registry (VOTOR), and electronic medical record (EMR) information (e.g. X-rays, surgical reports, radiology reports, images). A multimodal deep learning fracture reasoning system (DLFRS) will be developed that reasons on EMR information. Machine learning prediction models will test the performance with/without output from the DLFRS.

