While detailed fracture classifications exist, these are rarely documented in medical records, and administrative diagnostic coding fails to characterise fracture details sufficiently [29]. In addition, there is classification error generated randomly, due to (lack of) inter-observer reliability, coding and transcription errors. The International Statistical Classification of Diseases and Related Health Problems, Tenth Revision, Australian Modification (ICD-10-AM) includes limited information about key characteristics of the fracture. For example, one third of distal radius fractures in VOTOR receive the “not further specified” code by hospital coders and laterality (i.e. left or right) is not captured at all. Similarly, routine coding of the management of fractures is done through Australian Classification of Health Interventions (ACHI) which provide a broad overview of the management such as the type of reduction of the fracture (closed vs. open) and whether fixation was used (but not the type of fixation).

Compounding issues with characterising fracture characteristics is the lack of barcode-to-patient tracking mechanisms or mandatory reporting of issues with most implants (e.g., plates, screws, wires). The majority of fracture implants are exempt from the Therapeutic Goods Administration requirement to provide patient information leaflets. The lack of routine and systematic post-market surveillance, and standardised capture of implant data at a patient-level places a greater reliance on collecting data about the detailed management of the fracture from other sources. Mining the heterogenous health data which already exists, with modern AI may offer the solution to unravelling previously hidden fracture details and characteristics.

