### Study aims

There are three aims of the PRAISE study:

Develop valid and reliable algorithms for identifying key distal radius fracture characteristics and treatment details using NLP and deep machine learning techniques applied to digital images, and surgical and radiology text reports.Test whether AI derived fracture and treatment characteristics improve prediction of patient-reported outcome measures (PROMs) and clinical outcomes following distal radius fracture, compared to prediction models based on standard registry data.Establish the documenting and supporting code for deployment of the AI algorithms into health data platforms to enhance clinical registry data collection and availability of key data to clinicians.

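### Aim 2's single with/without contrast cannot by itself show that radiological fracture features improve prediction if AI-derived treatment is in the added block, and the article is inconsistent on whether it is

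*Protocol article*

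**What the plan says.** **The contrast.** The abstract states it as "Machine learning prediction models will test the performance with/without output from the DLFRS". The Aim 2 section says that performance measures will be used to "quantify the impact of the inclusion of the AI variables over registry data alone". Both describe one comparison of the AI variables, taken together, against the registry.

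**The added block.** Under Study aims, Aim 2 is to "Test whether AI derived fracture and treatment characteristics improve prediction of patient-reported outcome measures (PROMs) and clinical outcomes following distal radius fracture", so treatment is included. The Aim 2 section describes the addition more narrowly: "AI-derived fracture predicted probabilities and classes will be added to the VOTOR registry data and sent to the CVDL for the Linked VOTOR data". Treatment is not named there. The same section says "The capacity of the AI derived fracture characteristics to predict outcome compared to the Linked VOTOR registry data alone will be tested".

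**The inference.** Of this comparison the Aim 2 section says: "This will enable us to determine which radiological features based on the X-rays and text reports improve prediction over the standard data available in the" […].

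**The comparator.** ACHI codes give the type of reduction (closed or open) and "whether fixation was used (but not the type of fixation". The Aim 1 section describes the registry's implant data, taken from hospital ordering systems, as "complete for only 60% of surgical cases, and does not specifically link implants to injury".

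**The AI treatment output.** Aim 1 produces a five-category treatment class that separates external fixation, wires and plate.

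**The concern.** If the AI treatment class enters with the fracture features, the two models differ in two respects at once. One has fracture detail that the other lacks, and it also has fuller information on which fixation was used. A gain over registry data alone could come from either source.

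The two explanations have different consequences. A gain from fracture features would support the study's premise that fracture detail hidden in images and reports improves prediction. A gain from treatment recording could instead be met by better capture of implant data and would say little about the fracture itself. The planned contrast cannot tell them apart, yet the article states the fracture-specific conclusion as something the comparison will deliver.

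**Working it through.** The article gives no figure for the Aim 2 gain, so there is none to reproduce. Its only computed sample size, 517, belongs to Aim 1 and has no bearing here.

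**Step 1. What each model knows about treatment**

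| Item | Registry comparator | Added if AI treatment is in the block |
|---|---|---|
| Closed or open reduction | yes (ACHI) | yes |
| Fixation used or not | yes (ACHI) | yes |
| Type of fixation | not in ACHI; implant data complete for 60% of surgical cases, incomplete for 100 − 60 = 40%, and not tied to the injury | AI treatment class |

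**Step 2. What the contrast measures.** Let A be the performance of the registry model, B that of registry + AI treatment class, and D that of registry + AI treatment class + AI fracture features. Then

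D − A = (B − A) + (D − B).

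The article reports D − A. A statement about radiological fracture features needs D − B. The two agree only if B − A is zero, that is, if AI treatment adds nothing to the registry. Step 1 gives reason to doubt that.

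**Step 3. How large B − A could be.** All effect sizes here are assumptions; none is in the article.

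*Simulation 1.* 6,000 patients, half for training and half for testing, logistic models, 100 replicates. The outcome depends on one registry covariate and a binary fixation type, with no fracture effect. The AI fixation class is 90% accurate, 60% of patients have surgery, and fixation type is known to the registry in 60% of surgical cases. Mean test AUC:

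- Fixation odds ratio 3: A 0.647, B 0.654, D 0.653. D − A = 0.006; D − B = −0.001.
- Fixation odds ratio 8: A 0.720, B 0.733, D 0.733. D − A = 0.013; D − B = 0.000.

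Over odds ratios 2 to 8, D − A ran from 0.2 to 1.3 AUC points (1 point = 0.01).

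*Simulation 2.* 200,000 patients, half for training and half for testing, one run per scenario. Four treatment classes depend on three fracture features, and AI variables are taken as error-free. The comparator holds reduction type, fixation yes/no, and fixation type in a share c of surgical cases. Treatment affects the outcome in every row; the modest fracture effect is a log odds ratio of 0.2 per standard deviation of each feature.

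| c | Fracture effect | B − A | D − B | D − A |
|---|---|---|---|---|
| 0 | none | 0.0261 | −0.0007 | 0.0253 |
| 0.6 | none | 0.0145 | −0.0005 | 0.0140 |
| 0.9 | none | 0.0038 | −0.0012 | 0.0026 |
| 0.6 | modest | 0.0052 | 0.0500 | 0.0552 |

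At the article's 60% figure with no fracture effect, the block still gains 1.4 points, and fracture features add nothing beyond treatment. With a modest fracture effect, 0.0500 / 0.0552 = 91% of the gain is theirs. In both cases D − A is positive; only the split into B − A and D − B tells them apart.

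**Step 4. Fracture features as a proxy.** In simulation 2 with no fracture effect, fracture features added to the registry without AI treatment gained 0.0016 at c = 0.6 and 0.0051 at c = 0, because they partly stand in for the missing fixation type. The increment should therefore be taken over registry + AI treatment.

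**The case against.** **The Aim 2 methods name only fracture outputs as added.** This is correct, and on that wording the bundling does not arise. But the aim itself names treatment too, so the article does not settle the matter. Its description of the linked dataset includes treatment but does not say whether that is AI-derived. The inconsistency is part of the point.

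**On the wider wording, the contrast matches the aim.** This also stands. The full block against the registry is a valid answer to Aim 2 as worded. What does not follow is the further statement about which radiological features help.

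**Variable selection gives feature-level information.** It gives some, and the figure showing the approach is not available. But retention among correlated predictors, which the article itself says may give unstable estimates, does not measure performance gained over registry plus treatment.

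**Nested sets are analysis-plan detail.** Their absence alone would not be a finding. The point is that the article states a contrast and draws a conclusion that the contrast does not support.

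**Stronger readings that the article does not support.** A reader might infer that the registry largely lacks fixation type. It does not: implant data are complete for a majority of surgical cases, and the procedure codes carry part of the information. A reader might also infer that AI implant type enters the Aim 2 models, but it appears only as an Aim 1 output checked against registry data. Nor does the abstract's discussion credit fracture features alone; it speaks of AI-derived characteristics generally.

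**Conclusion.** The point holds conditionally. The content of the AI block is described inconsistently. If AI treatment class is in it, a gain over registry data alone cannot by itself show that radiological fracture features improve prediction, because the comparator holds fixation type only incompletely and unreliably.

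The size is uncertain. At 60% implant completeness with no fracture effect, the two simulations give a block gain of about 0.2 to 1.4 AUC points. It shrinks to about 0.3 at 90% completeness, and most of the gain stays with the fracture features when they have a modest effect. Gains of up to 7.3 points arose in simulation 1 only with no usable implant data and an odds ratio of 8; the article supports neither.

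It would be tempting to conclude that all of the gain would come from treatment recording, or that no gain can ever be credited to fracture features. The first is true only by construction, where the fracture effect is set to zero. The second ignores the planned variable selection. The overall Aim 2 comparison remains valid. The point warrants a change to the analysis and to one sentence.

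**What to change.** 1. Make Study aims and the Aim 2 section agree on what the AI block contains, and say explicitly whether AI treatment class is in it.
2. With the same algorithm, patients and train/test split, report nested predictor sets: registry; registry + AI treatment class; registry + AI treatment class + AI fracture features.
3. Keep the full block against the registry as the overall Aim 2 result.
4. Base the statement on which radiological features improve prediction on the increment over registry + AI treatment class. Otherwise, limit that sentence to the AI variables as a whole.

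The cost is wording and a few extra model fits per outcome and algorithm, with no new data. The drawback is that the gain credited to fracture features may be smaller than the bundled figure.
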